**Fig. 1 Fig1:**
[figure not shown]
Participants flow chart

### Sample size

A priori sample size estimation was made with the tool G*Power3.1 [20]. One-way ANOVA power analysis with three groups was based on the results of previous works [21]. The analysis considered that the groups receiving preoperative intervention will reach a score on the primary outcome the Berg Balance Scale of 53, this score being 5 points above that of the non-intervention group, with a reasonable standard deviation of 4.5 points, and with α = 0.05. The trial must consist of groups of 20 participants in order to achieve *d* > 0.8 and *f*
^2^ > 0.5. Predicting over 20% of sample loss, a total of 75 participants will be divided into 3 equal groups. Once data are collected, a post-hoc analysis will determine if the sample provided sufficient power to the trial.

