### Data analysis

The implementation of protocols will be presented with descriptive statistics. In an exploratory way, the drop-out ratios will be estimated and the survival analyses will be used [29]. This aspect will also be taken into account throughout the follow-up and registering when drop-outs occur. The incidence of adverse effects at 6 weeks will be evaluated, which will be categorized according to whether they are considered to be definitive, probable or possibly related to the interventions.

It is hypothesized that the experimental groups will have enhanced balance abilities, which may also have a direct impact on functionality in the short and mid-term. All temporal instants are of interest, although particular attention will be paid to the early postoperative effects (6w) and maintenance of potential mid-term benefits (1y).

The data analysis will include the sample descriptors, a comparison of the baseline condition with the t tests that will be parametric or not depending on the results of the tests of Wilcoxon and Shapiro-Wilk, and a comparison of the progress due to the results of the intervention with an ANOVA analysis of repeated measures, looking for interactions initially as a function of time, group, and time per group. In case of baseline differences between the participants, an ANCOVA analysis will be conducted instead, in which the data will be adjusted to the baseline scores. Analyses will be performed for primary and secondary outcomes. Post-hoc analyses will be performed accordingly. The significance levels will be set at 95%.

A qualitative analysis will be carried out in which it will be estimated if the obtained progressions measured as the mean values of the difference between the basal and final values for each variable at each time point reach the minimum established according to the psychometric properties referring to the minimum clinical importance difference or minimum detectable change with a CI of 95%, if they are available in the literature. If they had been reported by different studies, it would be based on the suggested minimum value.

A post-hoc power analysis and an estimate of the effect size will be implemented with the tool G*Power [20], based on Cohen’s *d* and considering a low, medium or high effect as a function of the result [30].

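### The sample-size paragraph reports f² > 0.5 where its own inputs give f = 0.52 and f² = 0.27 (the group size is unaffected), and the planned post-hoc power check, if based on the observed effect, only restates the p-value

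*Protocol article*

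**What the plan says.** The Sample size section of the protocol article names the method: "One-way ANOVA power analysis with three groups was based on the results of previous works". The two preoperative arms are expected to reach 53 on the Berg Balance Scale, "this score being 5 points above that of the non-intervention group, with a reasonable standard deviation of 4.5 points", "and with α = 0.05". The conclusion is then given in terms of effect size: "The trial must consist of groups of 20 participants in order to achieve" d > 0.8 and f² > 0.5. Twenty per group is raised to 75 in total to allow for a loss put at over 20%. The article prints no target power.

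The same section ends by saying that, once the data are in, "a post-hoc analysis will determine if the sample provided sufficient power to the trial". The Data analysis section returns to this: "A post-hoc power analysis and an estimate of the effect size will be implemented with the tool G*Power". It bases the work on Cohen's d, with the effect graded low, medium or high according to the result.

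**The concern.** There are two separate matters.

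First, the printed f² cannot be obtained from the means and SD in the sentence before it. A reader who takes f² = 0.5 as the planning effect cannot reproduce 20 per group. The wrong value could also be carried into the results paper.

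Second, the adequacy of the sample is to be judged after the fact by a power calculation. If that calculation uses the observed effect, it holds no information beyond the p-value, and every non-significant comparison will look underpowered. This matters here because the Background and Discussion also want to learn whether in-home training does as well as hospital training. That question may well end in a non-significant difference, and its answer depends on how large a difference the data still allow.

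**Working it through.** **Inputs (Sample size section).** Means 53, 53 and 48; SD 4.5; α = 0.05; three groups; 20 evaluable per group, so N = 60.

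**Step 1: effect size.**
- Grand mean = (53 + 53 + 48)/3 = 51.33
- SD of the means = √[(1.667² + 1.667² + 3.333²)/3] = √5.556 = 2.357
- f = 2.357/4.5 = 0.524, so f² = 0.274
- d = 5/4.5 = 1.11

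The stated d > 0.8 is satisfied. The stated f² > 0.5 is not, whereas f > 0.5 would be.

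**Step 2: could another definition give f² > 0.5?**
- d²/4 = 0.309
- Variance of the means with divisor k − 1, over SD²: 8.333/20.25 = 0.412
- η² = 0.274/1.274 = 0.215

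None reaches 0.5. To have f² = 0.5 (f = 0.707) with the same pattern of means, the difference would have to be 0.707 × 4.5 × 3/√2 = 6.75 points, or the SD would have to be 2.357/0.707 = 3.33.

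**Step 3: does the sample size reproduce?** Power comes from the noncentral F distribution with 2 and 57 degrees of freedom and λ = f²N = 0.2743 × 60 = 16.46.

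| Power sought at f = 0.524 | Smallest n per group |
|---|---|
| 80% | 13 |
| 90% | 17 |
| 95% | 20 (power 95.2%) |

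Allowing for loss: 60/(1 − 0.20) = 75, or 25 per group. The plan's 20 and 75 therefore follow from its means and SD at 95% power. Had f² = 0.5 been used, 12 per group would have sufficed for 95%, and 20 per group would give 99.9%. This supports the view that the calculation used f = 0.52 and that the symbol was misprinted.

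**Step 4: post-hoc power from the observed effect.** For a given p-value, take the F that produces it on 2 and 57 degrees of freedom, set f² = 2F/60 (or 2F/57, the other common estimate), and compute power at N = 60.

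| p-value | Observed power, f² = 2F/60 | Observed power, f² = 2F/57 |
|---|---|---|
| 0.01 | 79.3% | 81.5% |
| 0.05 | 58.3% | 60.7% |
| 0.20 | 33.5% | 35.1% |
| 0.50 | 16.3% | 16.9% |

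Nothing but p, N and the number of groups enters the calculation. Any p above 0.05 returns a power below about 61%.

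**The case against.** The strongest reply is that this is one wrong symbol with no effect on the design. That stands: the patient numbers are right for the stated means and SD, and nobody should infer from the f² error that the trial is too small or too large.

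A reader might also take d > 0.8, the means with their SD, and f² > 0.5 as three competing planning effects with very different powers. The text does not support that. The d is a lower bound that 1.11 meets, so it is not an alternative assumption; only f² contradicts the inputs. The missing target power is not a fault in itself in a condensed article. Nor does it matter that 25 per group covers exactly 20% loss where the text says over 20%.

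On post-hoc power, the article does not say outright that the observed effect will be used. Power recomputed at the planned 5 points with the achieved numbers would not be a restatement of p. The reference in Data analysis to Cohen's d and to grading by the result makes the observed-effect reading the likelier one, but not a certain one. The percentages in Step 4 also belong to a one-way F test with 60 participants, whereas the main analysis is a repeated-measures ANOVA, so they are illustrative.

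Finally, a reader might infer that the plan would excuse every null result or rule out confidence intervals. It says neither. Data analysis also plans effect sizes and a comparison of changes from baseline with published thresholds. That is a partial answer, since it does not address differences between arms.

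**Conclusion.** The concern holds as two limited corrections.

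- **Effect size.** The printed f² > 0.5 is wrong: the stated inputs give f² = 0.27 and f = 0.52. This rests only on the article's means and SD, with both preoperative arms at 53. The size of 20 per group and 75 in total stands. The 95% power is a recomputation, not a figure the article gives.
- **Post-hoc power.** As a test of whether the sample was sufficient it is a poor rule, provided it uses the observed effect. On that reading it adds nothing to the p-value and would call any non-significant result underpowered.

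**What to change.** 1. In Sample size, replace the two inequalities with d = 1.11 and f = 0.52 (f² = 0.27). State the power that 20 evaluable participants per group deliver: 95% by recomputation, for the sponsor to confirm.
2. Remove the post-hoc power analysis from Sample size and Data analysis. Keep the effect-size estimate, which shares the Data analysis sentence.
3. Add that non-significant results will be interpreted from the 95% confidence interval of the between-arm difference. For the Berg Balance Scale, set it against the 5-point planning difference. The co-primary KOOS ADL has no planning difference, so use the published minimal clinically important difference that Data analysis already intends to draw on, where one is available.

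The cost is a few changed sentences and a less favourable stated f². No extra patients are needed.

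### 75 enrolled leaves the required 20 per group only if the loss is at most 20%, yet the sample-size section predicts a loss above 20%

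*Protocol article*

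**What the plan says.** All the figures stand in the Sample size section of the protocol article. The calculation is a one-way ANOVA with three groups on the Berg Balance Scale. Both preoperative training groups are assumed to reach 53, "this score being 5 points above that of the non-intervention group", "with a reasonable standard deviation of 4.5 points", at a significance level of 0.05. The resulting requirement is "The trial must consist of groups of 20 participants". The allowance for loss follows: "Predicting over 20% of sample loss, a total of 75 participants will be divided into 3 equal groups".

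The section gives no exact loss rate, no upper limit for it, no inflation formula and no target power.

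**The concern.** The required group size, the predicted loss and the enrolled total are all printed, so this is not detail that a condensed article leaves to a fuller document. The three do not fit together. If the loss is above 20%, as predicted, 75 enrolled cannot leave 60.

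What is at stake is the accuracy of the published justification. A reader will take "Predicting over 20% of sample loss" to mean that the design holds its required size with something to spare beyond 20%. It holds it at 20% and no further: the 16th participant lost takes the trial below 60.

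**Working it through.** **Inputs, all from the Sample size section**
- Required after loss: 20 per group, so 3 × 20 = 60.
- Enrolled: 75 in three equal groups, so 25 per group.
- Predicted loss: above 20%, with no upper figure.
- Means 53, 53 and 48 (48 = 53 − 5); standard deviation 4.5; α = 0.05; one-way ANOVA with three groups.

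**Step 1: reproduce the enrolled total.** With loss rate L among those enrolled, enrolment = required / (1 − L). At L = 0.20, 60 / 0.80 = 75, or 20 / 0.80 = 25 per group. The match is exact, so 75 is the correct figure for a loss of 20%.

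**Step 2: look for a reading that fits a loss above 20%.** The extra participants number 75 − 60 = 15. As a share of those enrolled, 15 / 75 = 20%. As a share of the required 60, 15 / 60 = 25%. Only the second exceeds 20%, and it is an inflation factor, not a loss rate among those enrolled.

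**Step 3: what 75 leaves as the loss rises.** Remaining = 75 × (1 − L); the average per group is a third of that.

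| Loss | Remaining | Average per group |
|---|---|---|
| 20% | 60 | 20.0 |
| 21% | 59.25 | 19.75 |
| 25% | 56.25 | 18.75 |
| 30% | 52.5 | 17.5 |

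The plan names no rate above 20%, so every row after the first is a scenario.

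**Step 4: reproduce the 20 per group.** The grand mean is (53 + 53 + 48) / 3 = 51.33. The variance of the group means is (1.667² + 1.667² + 3.333²) / 3 = 5.556. Then f² = 5.556 / 4.5² = 0.274 and f = 0.524. With the noncentral F distribution on 2 and N − 3 degrees of freedom and noncentrality N × f², N = 60 gives noncentrality 16.46 and power 95.2%. Twenty per group is the smallest size that reaches 95% (19 per group gives 94.1%). A target of 95% is therefore plausible, but it is inferred. Thirteen per group would give 80.8%.

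**Step 5: power under the shortfall**, by the same formula with equal groups.

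| Completers | Power |
|---|---|
| 60 (20% loss) | 95.2% |
| 59 (16 lost) | 94.9% |
| 56.25 (25% loss) | 93.8% |
| 52.5 (30% loss) | 91.9% |

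The fractional completers are expected values. At whole counts of 56 and 52 the powers are 93.7% and 91.7%.

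**The case against.** The strongest reply is that 75 is right. It follows exactly from 60 / 0.80, a reserve of 15 participants is in place, and the quarrel is over one word in an open-ended phrase. No target power is stated, so none is missed, and the 16th loss costs about 0.3 percentage points (95.2% to 94.9%).

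Most of this stands. A reader might infer that the allowance for loss does not exist at all. The document does not support that: the whole of a 20% loss is covered, and only the part above 20% is not. That part cannot be sized, because the plan gives no upper rate.

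Three further inferences also go too far:
- **Power at d = 0.8.** Recomputing at that effect gives far lower power, but the section states 0.8 as a lower bound and its own inputs give 5 / 4.5 = 1.11. The drop would come from the smaller effect, not from the loss.
- **A required retention per visit.** The calculation is a one-way ANOVA and does not demand complete data at every visit. The section on missing data plans home completion of questionnaires, visits by the evaluator, and imputation.
- **Removals under the Participants section.** Moved surgery dates and postoperative complications may already be counted in the predicted loss. The document gives no rate for either.

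The reply does not remove the mismatch. No loss above 20% is compatible with 60 remaining out of 75.

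**Conclusion.** The point holds as a small inconsistency in a stated figure. Any loss within the plan's prediction takes the trial below its required 60, while a loss of up to 20% is fully covered. At the plan's means and standard deviation the cost in power is about 1.4 percentage points at a 25% loss (95.2% − 93.8%) and about 3 at 30%.

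This rests on reading the loss as a share of those enrolled, on losses that fall evenly across the groups, and on the plan's assumed difference and standard deviation. The two loss rates are assumptions chosen to show the range. The mismatch does not show that the trial is underpowered or should enrol more, and it affects no analysis.

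**What to change.** Correct the one sentence in the Sample size section, in either of two ways:
- say that 75 participants allow for a loss of up to 20% (15 participants), leaving on average 20 per group; or
- state the loss rate actually expected and the group size it leaves. For example, a 25% loss leaves about 18.75 per group.

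The words *on average* are needed because losses may split unevenly: 15 lost as 7, 4 and 4 leaves groups of 18, 21 and 21.

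The cost is one sentence and a slightly less favourable statement. Enrolment can stay at 75. If the authors preferred to keep 20 per group at a higher loss, equal whole groups would need 26 each (78) for 21% to 23% and 27 each (81) for 25%, but the small effect on power does not call for it.

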### Blinding and randomization

Participation occurs sequentially. At the time that a subject has an established date of operation, the physician checks the criteria are being met. If so, the potential participant is informed of the study and is referred to the rehabilitation department where, if is definitely admitted will take part in the randomization process. The randomization is generated from the output of the Matlab® statistical program by external assessor. A physiotherapist with 3 years of experience and blinded to the intervention groups will be in charge of the outcome assessment. The blinding of the participants is not assured, as they are informed about the trial before randomization. Neither is it the blinding of those who provide the treatments for the same reason. However, physiotherapists do not take part in the process of randomization and participant allocation. The external assessor in charge of the randomization is blinded to the intervention groups that have a numerical coding, and will receive the data of the participants for the statistical processing. The interpretation of the results will be carried out by the whole team.

### Interventions

The interventions are supervised by 2 physiotherapists with more than 15 and 20 years of experience. All groups perform the same postoperative intervention. This consists of a standard recovery program based on the Brotzman principles [22] and clinical experience, and have been pragmatically adapted to hospital standards according to the following aspects: muscular strengthening with isometric, isotonic, and resistance exercises, functional exercises, and to a lesser extent proprioception and balance exercises. The protocol consists of 3 phases: a warm-up phase with passive, active-assisted, and active mobilizations, a work phase with functional exercises for balance and strength, and a cooldown phase with relaxation activities. The sessions last approximately 60 min, and the loads are adapted to the possibilities of the subjects to avoid fatigue. A total of 12 sessions are prescribed, on alternate days, 3 times a week, and in a hospital setting. The intervention begins in week 2 and ends in week 6. In the case that the physician considers that a participant should perform a greater number of sessions, the standard hospital protocol continues. However, all participants are always evaluated after session 12 and during week 6, as the interventions may have influenced the early postoperative outcomes.

Preoperative and control interventions are detailed below, while the distribution of the interventions in groups are shown in Table 1.

**Table 1 Tab1:** Interventions and groups

Intervention/group	Non-active comparator	Experimental 1	Experimental 2
Preoperative			
In-hospital preoperative		x	
In-home preoperative			x
Postoperative			
Conventional physiotherapy	**x**	**x**	**x**

#### In-hospital supervised preoperative intervention (PRE_ EXP1)

Different exercises are proposed and developed over the course of the 12 sessions on alternate days, divided in 4 weeks of training. On the one hand the intervention includes a standard program of rehabilitation with strengthening exercises. In addition, each session includes a total of 4 to 5 balance and proprioceptive exercises performed over a period of 20 min. The training has been based on the Fitzgerald principles to train proprioception, on previous of our works, and on clinical experience [21, 23]. The first 2 weeks are oriented to enhance balance and proprioception with the side, treadmill, cross, and tandem walk exercises. These exercises are excluded in weeks 2 and 3 and multiple changes of direction, foam activities and balance work with the Bohler plate are performed instead. Also 5 min training of weight bearing and testing the limits of stability are performed during the last 4 sessions. Progression in the exercises is implemented as tolerated, always trying to avoid fatigue. The physiotherapist is responsible for recording attendance at rehabilitation sessions.

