Balance and proprioceptive approaches have been referred to as sensorimotor and neuromuscular trainings. A recent qualitative review suggested that these may be an acceptable adjunct to usual care in physiotherapy [13]. Nevertheless, the literature is scarce with respect to the impact of an additional training specifically oriented towards the recovery of balance and proprioception. Gstoettner et al. [5] suggested that balance and proprioceptive training is effective in improving standing balance, can avoid pathological gait patterns and falls, and proposed that further investigations were needed in order to give consistency to the findings. Later, Hubber et al. [14] and Villadsen et al. [15] evaluated the effects of a preoperative neuromuscular training program, while Fernandes et al. [16] analyzed the cost-effectiveness of the latter. None of them performed a comparative study between hospital and in-home intervention appraising the effects, pragmatism and costs.

With this background, this trial will determine the short and mid-term effects of a preoperative balance and proprioceptive training when conducted by patients undergoing total knee replacement, and the impact that this may have on the balance of the patient, functionality and quality of life [17]. Along with the effects, it is intended to determine whether in-home based training can be as effective as hospital training. The results will help to conclude whether the possible benefits may outweigh the health costs.

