#### In-home preoperative intervention (PRE_EXP2)

The in-home exercise program is essentially based on the same principles than PRE_EXP1, but adapted so it can be conducted at home. The first day is an education with the explanation of the exercises. The training is carried out in the hospital and is supervised by the physiotherapist. The participant is asked to repeat the exercises, and possible doubts are resolved. The intervention consists of a phase with exercises to strengthen the main musculature of the lower limb, and a second phase of balance and proprioceptive work. The muscular enhancement exercises are isometric quadriceps in extension, elevations of the lower limb with knee in extension, ankle in dorsal flexion, and slight hip flexion combined with abduction and adduction. Additionally, the middle gluteal and open chain quadriceps are also performed. Each set of exercises is performed in 4 series consisting of 10 repetitions with a rest of 90 s between each series. The proprioception exercises consisted of tandem position and walking, single-leg position, and treadmill walking. Each exercise has to be performed for 2–4 min. And the participants were asked to do so safely, for instance in a hallway or in front of a table or chair, to avoid falls. After session 6, the participant is appointed for a reminder and verification of exercises, as well as possible corrections in the implementation of the intervention. The participant is requested to register the number of sessions performed in a calendar. The physiotherapist phones the participants on a weekly basis, in order to check both the compliance of the program and the calendar fulfillment.

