#### Non-active preoperative intervention (PRE_NA)

In order to evaluate the true effect produced by the interventions, and to determine whether the postoperative results obtained are due to the appropriateness of the proposals, a non-active control group (third arm) was added.

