## Discussion

Total knee replacement is a surgical procedure with a high prevalence and associated health costs. The main objective is the elimination of pain and the maximization of the knee function. It is applied as the solution of severe osteoarthritis, a condition that greatly affects the proprioceptive system of the joint. The surgery involves greater deterioration, even when the posterior cruciate is preserved. Both the degeneration due to prolonged osteoarthritis and the procedure bears the consequence that, even after surgery, many limitations often persist [3, 4]. This bears a clinical impact on the balance abilities of the patient, which may be a direct cause of the functional limitations found [11, 12].

An early rehabilitation is essential, a continuous treatment when the subjects tolerate higher intensities is beneficial, and even when a muscular preconditioning is always recommended before any highly invasive surgery, there is still controversy about the effects in the total knee replacement outcomes. This is especially applicable if a cost-effective procedure is sought. For this reason, the use of a specific preoperative program have to be justified in economic terms, given the limitation of resources [7].

The design of this research will determine the effects and benefits of conducting training oriented towards balance and proprioception recovery, but also whether an in-home training can be as effective as a hospital supervised preparative training. While it is true that the inclusion of a control group renders the project implementation more arduous, it also makes it possible to determine the real effects of the experimental interventions. In addition, the costs of the in-home program are considerably lower than those of the hospital care. Therefore, a more cost-effective solution will be found if it is shown that in-home training achieves similar effects to the supervised one. The analysis will allow to ultimately conclude if, indeed, implementation costs are justified, and the proposal is applicable to clinical practice.

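### The stated aim is the effect of balance and proprioceptive training, but the three arms can only estimate a combined strengthening-plus-balance programme

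*Protocol article*

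**What the plan says.** **Aim.** The Background states that "this trial will determine the short and mid-term effects of a preoperative balance and proprioceptive training when conducted by patients undergoing total knee replacement". The Abstract says the same in shorter form. The Discussion repeats that "The design of this research will determine the effects and benefits of conducting training oriented towards balance and proprioception recovery". In reviewing the literature, the Background says evidence is scarce on "the impact of an additional training specifically oriented towards the recovery of balance and proprioception".

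**Hospital arm (PRE_EXP1).** "On the one hand the intervention includes a standard program of rehabilitation with strengthening exercises". The section then continues: "In addition, each session includes a total of 4 to 5 balance and proprioceptive exercises performed over a period of 20 min".

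**Home arm (PRE_EXP2).** "The intervention consists of a phase with exercises to strengthen the main musculature of the lower limb", followed by a second phase of balance and proprioceptive work. The participant also has a supervised education session, a check after session 6 and weekly phone calls.

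**Comparator (PRE_NA).** Table 1 marks no preoperative intervention for this arm, only the conventional postoperative physiotherapy that all arms share. Its stated purpose is "to determine whether the postoperative results obtained are due to the appropriateness of the proposals, a non-active control group" being added as a third arm.

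**Sample size.** The calculation assumes a Berg score of 53 in the trained groups, 5 points above the non-intervention group, with SD 4.5, α = 0.05 and 20 participants per group, raised to 75 in total for loss.

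**The concern.** The aim names one ingredient, but the arms vary a package. Read with the Background's remark about additional training, the question is what balance work contributes. Answering it needs two arms that differ in balance work and are otherwise alike. Here no arm receives strengthening without balance work.

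What is at stake is the conclusion the trial may draw. Under the aim as written, a positive result could be reported as evidence for balance training when strengthening, therapist contact or education may have produced some or all of it. A hospital that already offers preoperative strengthening could not tell from this trial whether a balance module is worth adding.

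**Working it through.** **1. What each arm receives before surgery**

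| Arm | Strengthening | Balance work | Contact or education |
|---|---|---|---|
| PRE_EXP1 | yes | yes | supervised sessions |
| PRE_EXP2 | yes | yes | education session, check, weekly calls |
| PRE_NA | no | no | none specified |

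Postoperative care is the same in all arms and cancels in every contrast.

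**2. What each contrast estimates.** Let S, B and C be the contributions of strengthening, balance work and contact in arm 1 (hospital) or arm 2 (home). Any interaction between components would only add unknowns.

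- PRE_EXP1 − PRE_NA = S1 + B1 + C1
- PRE_EXP2 − PRE_NA = S2 + B2 + C2
- PRE_EXP1 − PRE_EXP2 = (S1 − S2) + (B1 − B2) + (C1 − C2)

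The third line is the first minus the second, so there are two independent equations for six unknowns. B1 and B2 never appear alone. A total of 5 Berg points fits (S, B, C) = (0, 5, 0) and (5, 0, 0) equally well. The third line compares setting and supervision, with exercise content adapted to the home, and not balance work with its absence.

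**3. The planned size rests on the package effect.** Inputs from the Sample size section: means 53, 53 and 48, SD 4.5, α = 0.05.

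- Grand mean = (53 + 53 + 48)/3 = 51.33
- Between-group SD = √[(1.667² + 1.667² + 3.333²)/3] = √5.556 = 2.357
- f = 2.357/4.5 = 0.524
- One-way ANOVA, noncentral F, 20 per group: noncentrality 60 × 0.524² ≈ 16.5, power 0.952
- Inflation for loss: 60/(1 − 0.20) = 75

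The article gives no power figure. 20 per group is the smallest size reaching 95%; 80% needs 13 and 90% needs 17. The planned size is thus reproduced, and its 5-point input is trained versus non-intervention, that is S + B + C.

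**4. Illustration only: a balance-specific contrast.** The documents give no split of the 5 points, so the shares below are assumptions. Suppose a comparator with strengthening but no balance work, SD 4.5, two-sided α = 0.05, noncentral t with 2n − 2 degrees of freedom and noncentrality (δ/4.5)√(n/2).

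| Assumed balance share | δ (points) | Power at 20 per arm | n per arm for 80% power |
|---|---|---|---|
| 75% | 3.75 | 73% | 24 |
| 50% | 2.50 | 40% | 52 |
| 25% | 1.25 | 14% | 205 |

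This shows that the component question differs in size as well as in design. It is not a proposal to add such an arm.

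**The case against.** The strongest defence is that the protocol largely names the whole programme as its target. The Abstract's Methods set the effect of the proposal against the benefit of surgery alone. The PRE_NA section and the Discussion attach their claims of a genuine effect to the interventions. The Background describes a proposal seeking muscular and functional as well as sensorimotor gains, and the comparison it finds missing from earlier studies is hospital versus home, which these arms do address. Testing a multi-component programme against none is a legitimate pragmatic design, and the components are openly described.

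Most of this stands. It does not remove the mismatch, because the aim in the Abstract, Background and Discussion leaves out strengthening.

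A reader might go further in four ways that the documents do not support:

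- **That the claims about the true or real effect are wrong.** They refer to the interventions as wholes, which the design can estimate.
- **That the cost-effectiveness analysis misattributes the effect.** The Economic evaluation section compares whole experimental proposals with the non-active one and counts all costs potentially related to each, so costs and QALYs refer to the same package.
- **That balance work is a minor part of the programme.** Take four home strengthening exercises of four series, 3 s per repetition (assumed), and four balance exercises of 2–4 min. Strengthening then takes 8 min of work plus 18 min of rest, and balance 8–16 min. Balance is 8/34 to 16/42 (24–38%) with rests counted, or 8/16 to 16/24 (50–67%) without. The exercise counts are also uncertain, and time share says nothing about effect share.
- **That the parallel trial settles the component question.** The data-sharing section does not show that its conventional preoperative training matches the strengthening given here. Sharing is conditional on both trials finishing, and the pooled comparison is labelled PRE_EXP1 versus PRE_NA although the other trial's comparator is conventional training.

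Nor does the Background call preoperative strengthening advisable: it says so of a preoperative programme. The Discussion does recommend muscular preconditioning but reports controversy about its effect on knee replacement outcomes. Package versus nothing therefore remains an open question.

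**Conclusion.** The point holds in limited form. The aim in the Abstract, Background and Discussion is one the three arms cannot deliver. They can estimate the combined preoperative programme against none, and can compare its hospital and home forms. The balance component is not identified, so no numerical share of the 5-point Berg difference can be given. This follows from the arm descriptions and Table 1 and needs no outside figure; only the power illustration rests on assumed shares.

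This is a should-fix correction to the stated aim and the permitted conclusion. The arms, sample size, outcomes and planned analyses are not put in doubt by it.

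**What to change.** - In the Abstract, Background and Discussion, state the aim as the effect of a combined preoperative strengthening-plus-balance programme, in hospital or at home, versus no preoperative programme.
- Add one sentence saying that this trial will draw no conclusion about the added value of balance work alone.
- Mention the parallel trial as possibly informative on that component only if its conventional preoperative training is shown to match the strengthening given here. In the data-sharing section, reconcile the label PRE_EXP1 versus PRE_NA with that trial's conventional-training comparator.
- Leave the true-effect and real-effect phrases and the Economic evaluation section as they are.

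The cost is a few sentences. No arm, participant, measurement or analysis is added, and the only downside is a narrower headline claim.
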